#### Secondary outcomes

Secondary outcome measures are time until definitive treatment, quality of life, hospital-related healthcare costs and cost-effectiveness.

##### Time to definitive treatment

Time until definitive treatment is defined as the period between randomisation and TURBT for NMIBC and RC with or without NAC, or chemoradiotherapy for MIBC.

##### Quality of life

To assess generic health-related quality of life, the EuroQol 5 Dimension 5 Level (EQ-5D-5L) questionnaire^17^ will be administered to all participating patients on paper at baseline (inclusion in study), 6 months, 12 months and 24 months post-randomisation.

##### Hospital costs

Hospital registries will be used to identify all items, procedures and activities related to bladder cancer management to estimate the associated costs. Unit costs will be based on the guidelines outlined in the Dutch manual for costing studies.^18^ To obtain total costs per patient, resource use will be multiplied by the unit costs.

##### Cost-effectiveness

Cost-effectiveness will be analysed from a healthcare perspective, using a 2-year time horizon. Effectiveness will be measured in terms of quality-adjusted life years (QALYs), following the Dutch guideline for economic evaluation.^19^ QALYs will be based on the patient-reported EQ-5D-5L scores. From these scores, utility values will be calculated using the Dutch tariff.^20^ Based on these utility values, QALYs will be computed per patient using the area under the curve approach. Costs and QALYs in the second year of follow-up will be discounted at a rate of 3% and 1.5%, respectively, based on the Dutch guideline for economic evaluation. Absolute means and mean differences between the arms in terms of costs and QALYs will be calculated. As cost data are generally highly skewed, bootstrapping will be performed to estimate 95% CIs around the costs and effects.^21^ If the new strategy is both more costly and more effective, incremental cost-effectiveness ratios (ICERs) will be calculated by dividing the estimated differences in costs by the difference in QALYs. This will result in incremental costs per QALY gained. If the new strategy is less costly and more effective, it is considered to dominate the standard strategy. If it is less costly and less effective, ICERs will be calculated to derive the additional savings per QALY lost. If the new strategy is more costly and less effective, it is considered to be dominated by the current strategy. Cost-effectiveness acceptability curves will be derived, illustrating the probability of cost-effectiveness against different cost-effectiveness thresholds.^22^ All analyses will be performed on an intention-to-treat basis. The impact of missing data will be assessed with single imputation nested in the bootstrap percentile method.^23^

### Data collection methods

Data will be collected using standardised procedures to ensure consistency and accuracy across all participating centres. Clinical and imaging data, including mpMRI results and biopsy findings, will be recorded in the electronic data capture system CASTOR. Quality of life questionnaires (EQ-5D-5L) will be administered on paper, collected via mail and entered into CASTOR by trained study personnel. All data collection forms and procedures will be pilot-tested prior to study initiation to minimise missing data and measurement errors. Data collectors and outcome assessors will be trained and monitored regularly to maintain data quality.

### Harms

Adverse events (AEs) related to the study procedures will be recorded, but formal AE reporting is waived since both mpMRI with biopsy and TURBT are established, routine clinical procedures with well-known safety profiles. Serious adverse events (SAEs) that are unexpected and related to the study will be reported promptly to the accredited Medical Ethics Committee, except for SAEs expected as part of standard care (eg, haematuria following TURBT). All AEs will be monitored until resolution or stabilisation. A Data Safety Monitoring Board (DSMB) has been appointed to oversee patient safety throughout the trial. No interim safety analyses or early stopping rules are planned due to the low risk of harm. The sponsor will suspend the study and notify the ethics committee immediately if significant safety concerns arise.

### Participant timeline

**Figure 2 F2:**
[figure not shown]
Diagram of the schedule of enrolment, interventions and assessments. *Tx: moment of eligibility screen and signing informed consent; T0: randomisation and baseline questionnaire; Ty: mpMRI+biopsy (intervention arm) or TURBT (standard arm); T6: follow-up questionnaire at 6 months; T12: follow-up questionnaire at 12 months; T24: follow-up questionnaire at 24 months; Tz: close-out, including analyses of outcome measures, central pathology review. SAE monitoring is performed continuously throughout the study. Patients are not actively involved in the close-out. mpMRI, multiparametric MRI; SAE, serious adverse events; TURBT, transurethral resection of the bladder tumour.

The study timeline is as follows (see figure 2): month 1–6: to obtain formal approval of ethics committee and participating centres; month 7–42: patient recruitment, randomisation and intervention; months 7–66 follow-up period (at least 2 years); month 7–66: data collection including data on costs and EuroQol 5D-5L; month 67–72: data analysis and reporting. The study started in July 2023 and is expected to be completed at the end of 2029, including follow-up and final analyses.

### Sample size

The power calculation is based on an intention-to-treat (ITT) time-to-event analysis comparing PFS between the randomisation groups. The following parameters were used: alpha two-tailed=0.05, beta (1-power)=0.20 and 1:1 randomisation. Assuming a relative hazard of 0.55, 88 events are needed. With a baseline event rate of 0.23 per year in the TURBT group, a censoring rate of 0.1 per year, and an average follow-up period of 3.25 years, 117 participants are needed in each group. Despite the fact that adding NAC to RC only provides a 5–8% increase in overall survival after 5 years compared with RC alone, the presence of NAC (or chemoradiotherapy) might still alter the impact of TURBT on prognosis. Therefore, we will conduct a stratified analysis on RC alone vs other (systemic) treatment with curative intent. In the Netherlands, less than 15% of patients with cT2-4aN0M0 MIBC are treated with chemoradiation, a little over 20% with NAC and ~65% with RC alone. That means that 117/0.65=180 patients are needed in each arm. This sample size will provide us with the necessary power to analyse our primary research question in RC-alone patients effectively.

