**Methods and analysis:**

BladParadigm is a two-arm multicentre randomised controlled trial (RCT) conducted in the Netherlands. Over a 3-year period, patients with clinically suspected MIBC without evidence of metastases will be recruited and randomised 1:1 to either TURBT or 3-Tesla mpMRI with same-day outpatient bladder biopsy. The Vesical Imaging Reporting and Data System (VI-RADS) will be used to standardise mpMRI reporting. Patients will undergo definitive treatment based on the results of the TURBT or mpMRI. The study is powered to demonstrate that the mpMRI-based strategy is at least non-inferior to standard TURBT in patients treated with radical cystectomy alone, assuming a relative hazard of 0.55. The required sample size is 360 patients (180 TURBT, 180 mpMRI). The primary outcome is 2-year progression-free survival. Progression will be assessed by imaging, according to the current standard of care. Secondary outcome measures are time to definitive treatment, quality of life (EuroQol 5D-5L), healthcare costs and cost-effectiveness.

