##### Treatment and follow-up

Results from the mpMRI and biopsy are discussed in a multidisciplinary tumour board, where definitive treatment plans will be determined. Patients with a VI-RADS score of 1 or 2 will be classified as having NMIBC and will typically undergo TURBT, often supplemented by bladder instillations and/or re-TURBT. Those with a VI-RADS score of 3, 4 or 5 will be classified as having MIBC and will undergo definitive treatment, usually involving RC with or without NAC or chemoradiotherapy.

After treatment, all patients, including those in the standard care arm, will be monitored and progression will be assessed by imaging: (PET-)CT every 6 months until the third year, followed by an annual CT scan thereafter. The minimum follow-up duration for all participants in the study is 2 years from the point of randomisation. It is anticipated that patients enrolled earlier in the study can be monitored for a longer duration, potentially to 4.5 years, compared with those who enrol later.

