### Statistical methods

PFS (and TTP) in both trial arms will be compared in an ITT analysis using Kaplan-Meier curves and a log-rank test. In addition, we will use a proportional hazards regression model with the stratification factors (study centre and cystoscopy score 4/5) as covariates. In case of different distributions of other prognostic factors between both arms, despite the randomisation, we will adjust for these factors as well. Analyses will also be stratified by NAC (yes/no) and the Likert scale score following from visual inspection of the bladder during cystoscopy (score 4–5). We will not conduct any interim analyses.

We will compare the median time to definitive treatment between the two strategies using Kaplan-Meier analysis with a log-rank test. Missing data will be handled using multiple imputation with sensitivity analyses comparing imputed and complete case results. Prespecified subgroup and sensitivity analyses, for instance, stratified by use of neoadjuvant chemotherapy, will be conducted.

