To the best of our knowledge, the BladderPath study is the only other trial that is investigating an mpMRI-based diagnostic pathway for bladder cancer staging. Results on feasibility and time to correct therapy were recently published.^13 14^ The introduction of an MRI-based diagnostic approach led to a 45-day reduction in time to correct therapy. The findings from this study emphasise the importance of staging patients suspected of MIBC with mpMRI rather than TURBT. However, survival data were not evaluated due to insufficient enrolment due to the COVID-19 pandemic. To optimise our study design, we have consulted with the principal investigator of the BladderPath trial and made several adaptations, including the use of a 3T mpMRI (instead of a 1.5T mpMRI as done in the UK trial), evaluating PFS at 2 years after randomisation as our primary endpoint, and a more stringent selection of only patients with a suspicion of MIBC (Likert score 4 or 5 during cystoscopy, instead of all patients with gross haematuria). The latter, however, could also be considered a limitation, as cystoscopic-based assessment of potential muscle invasion is subject to variability and potential inaccuracies. This was shown in two studies on accuracy of cystoscopy where the prevalence of MIBC among patients with a Likert score of 4 or 5 was 72% and 78%, respectively.^26 27^

Equal to the BladderPath trial, follow-up will be at least 2 years for all patients. Given that most patients who experience progression will have progression in the first 2 years after radical treatment, 2 years is a sufficiently large time window for follow-up. It would be of added value to extend follow-up in this trial beyond 2 years to evaluate long-term results, but due to feasibility constraints, this was not possible. Patients will, however, be monitored long-term according to standard of care.

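### The primary outcome is labelled 2-year PFS, but the sample size and the described analysis use all follow-up (3.25 years on average), so the stated 80% power does not apply to a 2-year endpoint

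*Protocol article*

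**What the plan says.** Two horizons appear in the protocol article.

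**Two years.** The abstract says "The primary outcome is 2-year progression-free survival". The Objectives state the hypothesis in terms of 2-year PFS. The Primary outcome section opens by placing PFS at 2 years, and the Discussion twice describes 2-year PFS as the focus or primary endpoint. The Discussion also says it would add value to "extend follow-up in this trial beyond 2 years to evaluate long-term results, but due to feasibility constraints, this was not possible".

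**All available follow-up.** The Sample size section takes "alpha two-tailed=0.05, beta (1-power)=0.20 and 1:1 randomisation", then "Assuming a relative hazard of 0.55, 88 events are needed". It continues "With a baseline event rate of 0.23 per year in the TURBT group, a censoring rate of 0.1 per year", and ends with "an average follow-up period of 3.25 years, 117 participants are needed in each group". The 117 are patients treated with radical cystectomy (RC) alone. Dividing by 0.65 gives 180 per arm. The Primary outcome section defines PFS as a time from randomisation and censors event-free patients at their last assessment. Under Statistical methods, "PFS (and TTP) in both trial arms will be compared in an ITT analysis using Kaplan-Meier curves and a log-rank test". Under Treatment and follow-up, 2 years is the minimum, and "patients enrolled earlier in the study can be monitored for a longer duration, potentially to 4.5 years". The participant timeline runs follow-up over months 7 to 66.

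**The concern.** The primary outcome as named and the analysis as powered are different quantities. PFS at 2 years is a contrast at, or truncated at, a fixed time. An untruncated log-rank test with a hazard ratio summarises the whole curve, out to 4.5 years for some patients. If hazards are not proportional, for example because an early effect of the diagnostic route fades, the two can point to different conclusions.

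The stated 80% power belongs to only one of them. The article does not say which one carries the main conclusion. A reader of the final report could not tell from this document whether a 2-year difference or an all-follow-up hazard ratio was the pre-planned primary result.

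**Working it through.** **Inputs (all from Sample size).** Two-sided alpha 0.05, power 0.80, 1:1 allocation, hazard ratio 0.55, TURBT event rate 0.23 per year, censoring rate 0.1 per year, mean follow-up 3.25 years. The intervention event rate is 0.23 × 0.55 = 0.1265 per year.

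**Step 1: events needed (Schoenfeld).** 4 × (1.96 + 0.8416)² / (ln 0.55)² = 87.8, rounded up to 88. This matches the article.

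**Step 2: event probability by time T.** With constant event rate λ and censoring rate c, P(T) = λ/(λ+c) × (1 − exp(−(λ+c)T)).

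At T = 3.25:
- TURBT: 0.23/0.33 × (1 − exp(−1.0725)) = 0.4585
- mpMRI: 0.1265/0.2265 × (1 − exp(−0.7361)) = 0.2910
- n per group: 88/(0.4585 + 0.2910) = 117.4 (117.2 with the unrounded 87.8 events)
- events from 117 per group: 117 × 0.7495 = 87.7, power 79.9%

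The article's 88 events, 117 per group and 80% power are therefore reproduced.

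**Step 3: where 3.25 comes from.** (2 + 4.5)/2 = 3.25, the midpoint of the stated minimum and maximum follow-up. Spreading follow-up evenly over 2 to 4.5 years gives 86.5 events and 79.4% power. Recruitment in months 7 to 42 with follow-up to month 66 implies 2 to 5 years, which gives 90.0 events and 80.9%. Either way the all-follow-up analysis has about 80% power.

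**Step 4: the same inputs with every patient cut at T = 2.**
- TURBT: 0.23/0.33 × (1 − exp(−0.66)) = 0.337
- mpMRI: 0.1265/0.2265 × (1 − exp(−0.453)) = 0.204
- events from 117 per group: 117 × 0.5402 = 63.2
- power: Φ(√63.2/2 × 0.598 − 1.96) = Φ(0.416) = 66%

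Two simulations of 4,000 trials each gave 64% and 66% for the log-rank test truncated at 2 years, and 64% and 66% for the Kaplan-Meier difference at 2 years. The choice between these two forms of 2-year comparison therefore hardly matters here.

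**Step 5: range and scope.**

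| Analysis | Group | Events | Power |
|---|---|---|---|
| Mean 3.25 years | RC alone, 117 per group | 87.7 | 80% |
| Cut at 2 years | RC alone, 117 per group | 63.2 | 66% |
| Cut at 2 years, no censoring | RC alone, 117 per group | 69.3 | 70% |
| Mean 3.25 years | All randomised, 180 per arm | 134.9 | 93% |
| Cut at 2 years | All randomised, 180 per arm | 97.2 | 84% |

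The two rows for all randomised patients assume the same event rate and a hazard ratio of 0.55 in everyone.

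**Step 6: size needed at 2 years.** 88/0.5402 = 163 per group in the RC-alone stratum. By the article's own rule, 163/0.65 is about 251 per arm, against the planned 180.

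**The case against.** The strongest reply is that nothing is miscalculated. The PFS definition, the censoring rule, the log-rank test, the follow-up plan, the timeline and the sample size all agree with one another. Only the 2-year label is loose, and the 66% belongs to an analysis that no section specifies. This stands, and it sets the limits of the point. A reader might infer that the sample size section contains an arithmetic error, or that the trial simply has 66% power. The documents support neither: the 66% is conditional on a 2-year cut and concerns the RC-alone stratum.

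A reader might also take the Discussion to say that no follow-up past 2 years will take place. The same paragraph says follow-up will last at least 2 years for everyone, and other sections plan for more. The sentence plausibly means that the guaranteed minimum could not be extended. It needs rewording, but it is not an analysis rule.

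A third tempting step is to say that the constant hazard contradicts the Discussion's claim that most progression falls within 2 years. It does not. On the planning inputs, 63.2/87.7 = 72% of the planned events fall within 2 years and 28% later, and 72% is most of them. The Discussion also speaks of progression after radical treatment, whereas the calculation counts PFS events from randomisation.

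Finally, the intention-to-treat comparison of all 360 patients keeps about 84% power even at 2 years. That also stands, with two qualifications. The abstract and the Sample size section place the power claim in RC-alone patients. And the article itself allows that neoadjuvant chemotherapy or chemoradiotherapy may change the effect, so a common hazard ratio of 0.55 is an assumption.

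The SAP is not shown and may fix the data cut. That would not remove the difficulty, because the article already gives a primary outcome and a powered analysis that do not match.

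**Conclusion.** The concern holds as an inconsistency between the named primary outcome and the powered analysis. The figures of 88 events, 117 per group and 80% power are right for PFS over all follow-up. They are not right for a 2-year endpoint, where the article's own inputs give about 63 events and 66% power in the RC-alone stratum (about 70% without censoring). For all 360 patients, a 2-year cut gives about 97 events and 84%, provided the planning rate and hazard ratio apply to everyone. All these figures assume constant hazards, proportional effects and the stated censoring rate, except where no censoring is noted.

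The correction is one of wording. It matters because it settles which quantity the trial's main conclusion rests on.

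**What to change.** Choose one horizon and make the abstract, Objectives, Primary outcome, Sample size, Statistical methods and Discussion agree.

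**Preferred.** Define the primary outcome as PFS from randomisation over all follow-up to the common cut-off, tested as Statistical methods already describes. Report the Kaplan-Meier PFS at 2 years per arm, and its difference with a confidence interval, as a descriptive estimate. Reword the Discussion so that 2 years is the guaranteed minimum follow-up and not a limit. The sample size section then stands as written.

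**If 2 years stays primary.** Name the 2-year comparison in Statistical methods (truncated log-rank test or Kaplan-Meier difference at 2 years), and restate the RC-alone power as about 66% with about 63 events for 117 per group.

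**Cost.** Either route changes wording in the protocol and SAP, and in the registry entry if it carries the 2-year label (it was not available). The preferred route adds no patients or visits, because follow-up to month 66 is already planned. The second route adds none either, but the stated power becomes less favourable. Restoring 80% in the RC-alone stratum at 2 years would need about 251 per arm.

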##### Pathology review

All resected specimens from TURBT and cystectomy will be evaluated and reported by a urogenital pathologist, following standard protocols. At the end of the study, all specimens from the intervention arm—those obtained from TURBT (when mpMRI suggests NMIBC) and RC (without NAC, when mpMRI suggests MIBC)—will undergo central review to assess the diagnostic validity of mpMRI.

It is anticipated that mpMRI will classify a maximum of 10% of patients as NMIBC, who will then undergo TURBT. The remaining 90% of patients will be classified as MIBC, with approximately two-thirds of them treated with RC alone. As a result, a central pathology review will be conducted for approximately n=120 cases. As the central pathology review is performed at the end of the trial, results do not affect the choice of definitive treatment.

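### The step from 117 to 180 per arm applies a muscle-invasive-only share to everyone randomised, so power in RC-alone patients is about 66–77%, not 80%

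*Protocol article*

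**What the plan says.** The Sample size section of the Protocol article sets out a two-stage calculation. The first stage uses "alpha two-tailed=0.05, beta (1-power)=0.20 and 1:1 randomisation". For the effect size and the events it states: "Assuming a relative hazard of 0.55, 88 events are needed". The conversion from events to patients rests on these rates: "With a baseline event rate of 0.23 per year in the TURBT group, a censoring rate of 0.1 per year". Mean follow-up is put at 3.25 years, and the result is 117 per arm.

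The second stage inflates this number so that the RC-alone stratum carries the power. The share used comes from a sentence on Dutch practice, whose last figure refers to cystectomy without systemic treatment: "In the Netherlands, less than 15% of patients with cT2-4aN0M0 MIBC are treated with chemoradiation, a little over 20% with NAC and ~65% with RC". The inflation itself reads: "That means that 117/0.65=180 patients are needed in each arm". The section closes by claiming that this size gives adequate power for the primary question in RC-alone patients. The Abstract likewise says that the study is powered in that group.

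Three other places bear on the inflation:
- Inclusion criteria: entry requires a cystoscopy Likert score of 4 or 5, which is a suspicion of MIBC and not a confirmed stage.
- Discussion, on two accuracy studies: "the prevalence of MIBC among patients with a Likert score of 4 or 5 was 72% and 78%, respectively". The Discussion then adopts 72–78% as the pre-test probability in this trial's own population. It also gives sensitivity 92% and specificity 84% for VI-RADS 3–5.
- Pathology review: "It is anticipated that mpMRI will classify a maximum of 10% of patients as NMIBC, who will then undergo TURBT". The other 90% are to be classified as MIBC, about two-thirds of them having RC alone.

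**The concern.** The 65% has confirmed cT2-4aN0M0 MIBC as its denominator, while the 180 are patients with suspected MIBC. The product 180 × 0.65 = 117 is right only if every randomised patient has MIBC, or if patients with NMIBC have RC alone at the same 65% rate. The article claims neither. Under Standard of care and under Treatment and follow-up, NMIBC patients usually go to TURBT, with or without instillations.

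At stake is the power claim that the Abstract and Sample size section make for RC-alone patients. If it is too high, a null result in that group would be read as coming from a comparison with a 20% chance of missing a hazard ratio of 0.55, when the true chance is between about 23% and 34%. A second inconsistency follows: Pathology review and the Discussion imply different NMIBC shares for the same trial.

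**Working it through.** **Reproducing the stated figures.** Inputs are all from Sample size: two-sided alpha 0.05, power 0.80, 1:1, hazard ratio 0.55, TURBT event rate 0.23 per year, censoring 0.10 per year, follow-up 3.25 years.

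- Events (Schoenfeld): 4 × (1.960 + 0.842)² / (ln 0.55)² = 87.84, so 88.
- Probability of an observed event: λ/(λ + c) × [1 − exp(−(λ + c) × 3.25)]. With c = 0.10, λ = 0.23 gives 0.4585 and λ = 0.23 × 0.55 = 0.1265 gives 0.2910.
- Patients per arm: 88 / (0.4585 + 0.2910) = 117.4, stated as 117. Power at 117 per arm is 79.9%.
- Inflation: 117 / 0.65 = 180.0.

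The arithmetic is correct throughout. The fault lies in what the 0.65 is a share of.

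**RC-alone patients from 180 per arm, with MIBC prevalence p.**

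- TURBT arm: 180 × p × 0.65.
- mpMRI arm, VI-RADS positives only: 180 × [0.92p + 0.16(1 − p)] × 0.65.
- mpMRI arm, adding false negatives found to be MIBC at the later TURBT, as the Discussion describes: 180 × [p + 0.16(1 − p)] × 0.65.
- Pathology review figures, applied to both arms: 180 × 0.90 × 0.65 = 105.3, or 180 × 0.90 × 2/3 = 108.

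Events are D = 0.4585 × (TURBT number) + 0.2910 × (mpMRI number). Power is Φ(√D/2 × 0.5978 − 1.960).

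| MIBC basis | TURBT arm | mpMRI arm | Events | Power |
|---|---|---|---|---|
| 72%, positives only | 84.2 | 82.7 | 62.7 | 65.8% |
| 72%, plus false negatives | 84.2 | 89.5 | 64.7 | 67.1% |
| 78%, positives only | 91.3 | 88.1 | 67.5 | 69.0% |
| 78%, plus false negatives | 91.3 | 95.4 | 69.6 | 70.3% |
| 90%, RC-alone 0.65 | 105.3 | 105.3 | 78.9 | 75.7% |
| 90%, RC-alone two-thirds | 108 | 108 | 80.9 | 76.7% |
| 100% (implied by 117/0.65) | 117 | 117 | 87.7 | 79.9% |

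The 90% is stated for the intervention arm only. Using it there and 72–78% in the TURBT arm gives about 70–72%.

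For scale, 117 RC-alone patients per arm would correspond to 117/(0.65 × 0.78) = 231 to 117/(0.65 × 0.72) = 250 randomised per arm, or 117/(0.65 × 0.90) = 200 on the 90% figure.

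**The 10% figure against the Discussion.** The share classified NMIBC is 0.08p + 0.84(1 − p) = 0.84 − 0.76p. This is 29.3% at p = 0.72 and 24.7% at p = 0.78. Setting it to 10% requires p = 0.74/0.76 = 97.4%. The Discussion relies on these same inputs: they give positive predictive values of 0.6624/0.7072 = 93.7% and 0.7176/0.7528 = 95.3%, against its stated 93.6–95.4%.

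**Specimens for central review.** The 10%/90% split gives 18 + 108 = 126 (stated as about 120). The 25–29% share gives about 133–138, depending on p and on whether 0.65 or two-thirds is used.

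**The case against.** **The main analysis is intention-to-treat in all 360.** This stands as a limit. At the stated rates and hazard ratio, 360 patients give about 135 events and 93% power. A reader might infer that the trial as a whole is underpowered, and the article does not support that. The 93% does assume a hazard ratio of 0.55 and the same event rates in everyone, including NMIBC patients, who have TURBT in both arms; dilution would lower it. How far cannot be computed, because the article gives no NMIBC event rate. The intention-to-treat figure does not rescue the statement at issue, since both the Abstract and Sample size place the power in RC-alone patients.

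**The 72–78% scenario is not the only one.** Correct. A reader might take 66–69% as the result, but that ignores the 90% in Pathology review, under which the gap is only 3 to 4 points. It also leaves out understaged patients whom the later TURBT would identify.

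**Some NMIBC patients have cystectomy.** The Discussion says this is not uncommon for aggressive-looking tumours, so it would be too strong to say that no NMIBC patient enters the RC-alone group. The count would rise by an unquantified amount. Closing the gap fully in the TURBT arm means solving 180 × [0.65p + x(1 − p)] = 117, which gives x = 0.65 for any p: RC alone as often in NMIBC as in MIBC. The article does not suggest that.

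**The accuracy inputs come from one meta-analysis.** True, and the mpMRI-arm counts move with them. The TURBT-arm counts do not depend on them. The conflict over 10% survives other accuracy figures in the Discussion (sensitivity 87–91%, specificity 82–97%). The combination that classifies the fewest as NMIBC, 91% and 82% at p = 0.78, gives 1 − (0.91 × 0.78 + 0.18 × 0.22) = 25%.

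**Conclusion.** The concern holds for the RC-alone comparison. The inflation uses a share with the wrong denominator, and none of the MIBC shares in the article turns 180 randomised into 117 RC-alone patients. The supportable range is about 83–108 RC-alone patients per arm, 63–81 events and 66–77% power at a hazard ratio of 0.55. The lower part rests on 72–78% prevalence with 92%/84% accuracy, the upper part on the 90% in Pathology review. All of it rests on the article's own event, censoring and follow-up figures and on a 65% (or two-thirds) RC-alone share within MIBC. Cystectomy in NMIBC would narrow the gap by an amount that the article does not state.

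Separately, an NMIBC share of at most 10% cannot stand beside the Discussion's inputs, which imply about 25–29%.

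**What to change.** Keep 360 patients and correct the text:

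1. State one expected NMIBC share among randomised patients, with its basis, and use it in both Sample size and Pathology review.
2. In Sample size, replace the claim of 117 per arm and 80% with the RC-alone numbers, events and power over the plausible range (about 66–77% at a hazard ratio of 0.55). Say whether understaged patients and NMIBC cystectomies are counted.
3. Make the power statement in the Abstract agree.
4. Report separately the power of the all-randomised intention-to-treat comparison with its assumptions: about 93% only if the hazard ratio and event rates hold in everyone, and lower if NMIBC patients dilute the effect. Any figure for the diluted case needs an assumed NMIBC event rate and should be labelled illustrative.
5. Revise the 10%, 90% and n = 120 figures in Pathology review to match.

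The cost is a change of text only, with no change to recruitment or conduct. The downside is that the stated power becomes less favourable.

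### The primary question is powered in patients treated with radical cystectomy alone, a group formed after randomisation; this conflicts with the planned intention-to-treat comparison, and the 80% power claimed for that group does not hold

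*Protocol article*

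**What the plan says.** The Sample size section opens with the randomised comparison: "The power calculation is based on an intention-to-treat (ITT) time-to-event analysis comparing PFS between the randomisation groups". Its parameters are "alpha two-tailed=0.05, beta (1-power)=0.20 and 1:1 randomisation". It continues "Assuming a relative hazard of 0.55, 88 events are needed". The TURBT-arm rate is set at 0.23 events yearly; adding to this "a censoring rate of 0.1 per year, and an average follow-up period of 3.25 years, 117 participants are needed in each group". It next gives the Dutch treatment mix among patients with cT2-4aN0M0 muscle-invasive bladder cancer (MIBC), about 65% of whom have RC alone. It divides 117 by 0.65 to reach 180 per arm and ends: "This sample size will provide us with the necessary power to analyse our primary research question in RC-alone patients effectively". The Abstract likewise says the study is powered in patients treated with RC alone.

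Statistical methods plans an ITT comparison of progression-free survival (PFS) in both arms, and adds: "Analyses will also be stratified by NAC (yes/no".

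In the TURBT arm, definitive treatment follows the TURBT pathology (Standard of care: TURBT). In the mpMRI arm: "Those with a VI-RADS score of 3, 4 or 5 will be classified as having MIBC and will undergo definitive treatment" (Treatment and follow-up). Randomisation is stratified by centre and cystoscopy Likert score, not by intended treatment.

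**The concern.** One section names two populations for the powered comparison: all randomised patients in its first sentence and RC-alone patients in its last. The rise from 117 to 180 per arm has no stated purpose other than the RC-alone comparison, so the last sentence is not a slip of wording.

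The second population is a consequence of the allocated pathway. Each arm uses a different test to decide who has MIBC, and an unblinded tumour board then decides who has RC alone. Randomisation does not balance groups selected in this way, so the RC-alone hazard ratio can differ from 1 even if the pathway has no effect on progression. If the RC-alone result were reported as the answer to the primary question, a practice-changing claim would rest on a non-randomised contrast.

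**Working it through.** **1. The plan's own figures.** Schoenfeld events: 4 × (1.960 + 0.842)² / (ln 0.55)² = 87.8, so 88. The event probability per arm is λ/(λ+c) × [1 − exp(−(λ+c)T)], with c = 0.1 and T = 3.25. For λ = 0.23 it is 0.4585. For λ = 0.23 × 0.55 = 0.1265 it is 0.2910. The mean is 0.3747, and 88 / 0.3747 / 2 = 117.4 per group. Finally 117 / 0.65 = 180. All three stated figures reproduce.

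**2. What the division by 0.65 assumes.** It yields 117 RC-alone patients per arm only if all 180 are managed as MIBC. The document does not expect this. The Discussion puts MIBC prevalence at Likert 4–5 at 72% and 78%, and Pathology review expects about 90% of the mpMRI arm to be classified MIBC.

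**3. Expected RC-alone numbers.**
- TURBT arm, assuming that pathology finds all MIBC and nobody else has RC: 180 × 0.72 × 0.65 = 84 to 180 × 0.78 × 0.65 = 91.
- mpMRI arm at sensitivity 92% and specificity 84% (Discussion): the proportion called MIBC is 0.72 × 0.92 + 0.28 × 0.16 = 0.707, or 0.78 × 0.92 + 0.22 × 0.16 = 0.753. This gives 83–88 patients, or 89–95 if every false negative is found at the later TURBT and re-enters.
- mpMRI arm at the anticipated 90%: 180 × 0.90 × 0.65 = 105, or 108 with the two-thirds share used in Pathology review.

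**4. Power in RC-alone patients.** Power = Φ(√(d·a(1−a)) × |ln 0.55| − 1.96), where d is events and a is the TURBT share.
- Lowest case: d = 84.2 × 0.4585 + 82.7 × 0.2910 = 62.7, power 66%.
- Highest case: d = 91.3 × 0.4585 + 108 × 0.2910 = 73.3, power 72%.
- If the 90% figure held in both arms (105.3 each), d = 78.9 and power would be about 76%, still below 80%.
- For 117 RC-alone patients in the TURBT arm, 117 / (0.78 × 0.65) = 231 to 117 / (0.72 × 0.65) = 250 per arm would be needed.

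**5. Case mix in the RC-alone group.** At the stated accuracy, the non-MIBC share of the mpMRI group is 0.0448 / 0.7072 = 6.3% at 72% prevalence and 0.0352 / 0.7528 = 4.7% at 78%. With all false negatives returned it is 5.9% and 4.3%. The document gives no event rate for non-muscle-invasive disease, so a range of 0.05–0.10 per year is assumed, against 0.23 for MIBC. A simulation with no true effect and a TURBT stratum that is all MIBC gave RC-alone hazard ratios of 0.942–0.972, or 0.945–0.970 with false negatives returned. As a rough check, the average-hazard ratio (1 − f) + f × λ/0.23 is 0.950 at f = 6.3% with λ = 0.05, and 0.974 at f = 4.7% with λ = 0.10.

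**6. A selection effect in the other direction.** Patients must be event-free until RC, and the pathway is meant to shorten that wait. With assumed waits of 3 and 1.5 months, the simulated hazard ratio rises by about 0.06–0.08, to 1.003–1.042 net.

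**7. The ITT comparison at 360.** On the plan's rates, d = 180 × (0.4585 + 0.2910) = 134.9 and power at 0.55 is 93%. If only true MIBC contributes events and the hazard ratio is 0.55 in those patients, d = 97 at 72% prevalence and 105 at 78%, with power 84% and 87%.

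**The case against.** The strongest reply is that the planned main comparison is already ITT. PFS is defined from randomisation, Statistical methods compares the arms as randomised, and RC-alone enters the Sample size section as a stratified analysis for which the sample was enlarged. This stands, and it limits the point: a reader might infer that the trial's main analysis is not randomised, and the document does not support that. It does not remove the conflict, because the Abstract and the Sample size section still attach the powered question to RC-alone patients.

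A reader might also infer a large bias. Combining the anticipated 90% classified MIBC with 72–78% prevalence gives null hazard ratios of 0.78–0.90. But 90% needs a specificity of about 15–17% at sensitivity 92%, or 36–45% at sensitivity 100%, against the stated 84%. Those inputs do not fit together and do not show the likely size.

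Three further points soften the contrast:
- MIBC missed by mpMRI goes to TURBT, where the Discussion expects it can be detected, so it is not simply lost from the RC-alone group.
- The Discussion also says RC is not uncommon for aggressive-looking tumours without confirmed muscle invasion. If 10% of TURBT-arm non-muscle-invasive cases had RC (an assumption), the null hazard ratio would be 0.97–0.99.
- The two modelled biases nearly cancel. That is not reassurance either: the waits are assumed, and few progression events would be recorded before RC when patients enter without metastases on imaging and progression imaging follows treatment.

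Finally, the NAC yes/no split might be read as contradicting the RC-alone versus other split. It can equally be an additional analysis, so no contradiction is claimed.

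**Conclusion.** The point holds in a limited form. The document places its powered primary question in a group defined after randomisation by arm-specific staging, and so contradicts its own ITT comparison, which remains sound.

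The bias in the RC-alone contrast has no size or sign that the document can fix. Case mix alone suggests about 0.94–0.97 under the null, resting on the assumed non-muscle-invasive event rate and an all-MIBC TURBT stratum; other selection effects may offset it.

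Separately, 80% power in RC-alone patients is not supported. It is about 66–72% at a hazard ratio of 0.55, given 72–78% prevalence, TURBT pathology that finds all MIBC, and the plan's event and censoring rates. The arithmetic to 88, 117 and 180 is correct; what fails is applying a share among MIBC patients to everyone randomised.

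**What to change.** Name PFS in all 360 randomised patients, analysed as allocated, as the single primary and powered analysis. Restate its power: about 93% at a hazard ratio of 0.55 on the plan's rates, and 84–87% if only true MIBC contributes events. Delete the closing sentence of the Sample size section and the matching words in the Abstract. Label the RC-alone and NAC analyses exploratory and non-randomised.

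This needs wording changes in the protocol and, where it repeats the claim, the statistical analysis plan. No extra patients are needed. The cost is that the RC-alone claim is downgraded.
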